### Procedures

#### Recruitment

Participants will be recruited by open advertisement in newspapers, online, and notice boards at hospitals. Those who see the trial poster will visit the trial site voluntarily.

#### Study schedule

The detailed items that will be measured at every visit are described in Table 2.

**Table 2 T2:** A brief study schedule at every visit

	**Visit 0 (screening visit)**	**Visit 1 (1 month)**	**Visit 2 (3 month)**	**Visit 3 (6 month)**	**Visit 4 (12 month)**
Informed consent form	•				
Recording demographic data	•				
Medical history taking	•				
Physical examination^1^	•	•	•	•	•
FPG	•	•	•	•	•
OGTT	•	•	•	•	•
Serum insulin	•	•	•	•	•
Lipid profile^2^	•	•	•	•	•
HbA1c	•	•	•	•	•
Serum zinc	•	•	•	•	•
Liver function^3^	•			•	•
Renal function^4^	•			•	•
FBC^5^	•	•	•	•	•
Blood pressure	•	•	•	•	•
Electrocardiogram	•				•
Food frequency questionnaire	•	•	•	•	•
Appetite (VAS)	•	•	•	•	•

^1^Body weight, height, waist circumference and hip circumference; ^2^total cholesterol, triglyceride, LDL cholesterol, and HDL cholesterol; ^3^AST, ALT, g-GTP, total bilirubin, albumin, and total protein; ^4^creatinine and blood urea nitrogen (BUN); ^5^WBC, RBC, hemoglobin (Hb), hematocrit, and platelet count.

### Measurement tools

#### Anthropometric measurements

Body weight will be measured using a calibrated electronic floor scale (SECA 815 by SECA GmbH & Co. Kg., Hamburg, Germany) to the nearest 0.1 kg. Height will be measured to the nearest 0.1 cm using an upright plastic portable Stadiometer (SECA 217 by SECA GmbH & Co. Kg., Hamburg, Germany). BMI will be calculated as weight (in kilograms) divided by the square of height (in meters). Waist circumference (WC) will be measured with a non-elastic tape (SECA 203 by SECA GmbH & Co. Kg., Hamburg, Germany) at a point midway between the lower border of the rib cage and the iliac crest at the end of normal expiration. Similarly, the hip circumference also will be measured at the widest part of the buttocks atthe intertrochanteric level to the nearest 0.1 cm. All anthropometric measurements will be made by using standard equipment and following WHO guidelines.

#### Dietary measurements

A culturally validated FFQ will be used to obtain habitual intake of calorie, macro- and micronutrients [17]. A VAS, 10 cm in length with words anchored at each end, expressing the most positive and the most negative rating, will be used to assess hunger, satiety, fullness, and desire to eat.

### Compliance calculation

Subjects are asked to return remaining drugs and their compliance will be evaluated by using the formula given below:

$$\mathrm{Compliance}\left(\%\right)=\left[\frac{\left(\mathrm{distributed}\;\mathrm{drugs}-\mathrm{remaining}\;\mathrm{drugs}\right)}{\mathrm{distributed}\;\mathrm{drugs}}\right]\times 100$$

### Statistical analysis

Parametric and nonparametric statistical tests will be applied using SPSS version 16 (SPSS Inc., Chicago, IL, USA) and Stata/SE 10.0 (StataCorp., College Station, TX, USA) for the data analysis. For each of the outcomes, multilevel regression analysis will be used to examine differences between trial arms. For binary outcomes the model will be logistic and for continuous outcomes the model will be linear regression. All analyses will follow intention-to-treat principles and a pre-specified analysis plan. Where appropriate, sensitivity analyses will be conducted (for example, control for additional covariates and bootstrapped p values for skewed outcomes). In the case of missing data values, we will apply mean imputation and regression imputation where rates are low and consider multiple imputations where they exceed 10%.

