### Sample size

The number of patients required for determination of a 20% reduction of fasting plasma glucose in the treatment arm in comparison with the placebo arm at 90% power and 95% confidence interval with a dropout rate of 30% is 100 patients per arm. Hence, a total of 200 subjects with pre-diabetes will be recruited for the study.

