#### Suspension criteria

•Subject’s demand to discontinue the study.

•Serious adverse events or unusual changes in clinical test results.

•Principal investigator’s decision to terminate the study (low rates of compliance, complications, or unable to sustain the study for various reasons).

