### Randomization

Subjects will be stratified according to age, gender, and body mass index and randomly assigned into the test and placebo groups at a 1:1 ratio according to the ‘random number table’ generated by SPSS v16.0 software package (SPSS Inc., Chicago, IL, USA).

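### Outcome gaps are to be filled by mean or single regression imputation at low missing rates, and no method is committed at the 30% dropout the trial plans for

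*Protocol article*

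**What the plan says.** The Statistical analysis section sets out two tiers. For the lower it says: "In the case of missing data values, we will apply mean imputation and regression imputation where rates are low". For the upper, the same sentence says the team will "consider multiple imputations where they exceed 10" per cent. The boundary of the lower tier is therefore 10% by implication only. The article does not say which of the two single-imputation methods applies when, whether filling is done within arm, which predictors a regression would use, or whether a random residual is added.

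Three other statements bear on this:

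- The Sample size section gives the number needed "with a dropout rate of 30% is 100 patients per arm".
- The Outcomes section schedules measurement at five visits (0, 1, 3, 6 and 12 months) and bases the primary comparison on the change from visit 0 to visit 4.
- The Statistical analysis section names multilevel regression, linear for continuous outcomes, as the model for comparing arms, under intention to treat.

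**The concern.** A filled-in value carries no new information about the participant, yet the analysis counts it as an observation. What goes wrong depends on how it is filled. Within arm, the arm difference is kept but the data look larger and less variable than they are. Across arms, the filled values are the same in expectation in both arms and dilute the difference. Because the article leaves this open, even the direction of the error is not settled in advance.

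The second problem is where the trial expects to be. It allows for 30% dropout, three times the boundary at which single imputation gives way. At that rate the text promises no method; it promises to think about one. At stake are the width of the confidence intervals, the type I error or the size of the reported effect, and a missing-data rule that could be chosen after the extent of loss is known.

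**Working it through.** **Inputs from the article.** 100 per arm, 1:1 allocation, 30% dropout, 90% power and 95% confidence (taken as two-sided 5%, since sidedness is not stated), and a 10% boundary between tiers.

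**The plan's own figure.** 70 / (1 − 0.30) = 100 per arm, so the dropout step is consistent with 70 evaluable per arm. No SD is stated, so the 70 cannot be rebuilt. It implies a standardised difference of (1.960 + 1.282) × √(2/70) = 0.548, used below only to set a scale.

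**Which tier applies.** If those who drop out miss visit 4, month-12 missingness is 30% against a boundary of 10%. The planned case falls in the upper tier.

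**Lower tier, filling by arm mean.** Let m be the missing fraction and N the number per arm.

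- Apparent SE: SD × √(1 − m) × √(2/N), because the filled values add no spread but are counted in N.
- True SE: SD × √(2 / [N(1 − m)]).
- Ratio: √(1 − m) × √(1 − m) = 1 − m.
- Actual type I error: 2 × [1 − Φ(1.96 × (1 − m))].
- At m = 0.05: 1.96 × 0.95 = 1.862, giving 6.3%.
- At m = 0.10: 1.96 × 0.90 = 1.764, giving 7.8%.

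**Lower tier, filling by the overall mean.** With equal loss in both arms, the expected difference is (1 − m) × effect + m × 0 = (1 − m) × effect. At m = 0.05: 0.95 × 0.548 = 0.521. At m = 0.10: 0.90 × 0.548 = 0.493.

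**Check by simulation.** 100 per arm, 10,000 runs per scenario, analysis of covariance on baseline. Assumed: baseline–outcome correlation 0.5, data missing completely at random and equally by arm, regression filling on baseline without a residual draw. The Monte Carlo error on a 5% rate is √(0.05 × 0.95 / 10,000) = 0.2 percentage points. The SE ratio and type I error come from runs with no effect, and the mean estimate from runs with a true effect of 0.548.

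| Missing | Handling | Model SE / true SE | Type I error | Mean estimate |
|---|---|---|---|---|
| 5% | Observed cases only | 0.997 | 4.9% | 0.550 |
| 5% | Arm mean | 0.948 | 6.4% | 0.550 |
| 5% | Regression with arm | 0.947 | 6.5% | 0.550 |
| 5% | Overall mean | 0.998 | 5.0% | 0.522 |
| 5% | Regression without arm | 0.997 | 4.9% | 0.522 |
| 10% | Observed cases only | 1.006 | 4.9% | 0.550 |
| 10% | Arm mean | 0.903 | 7.6% | 0.549 |
| 10% | Regression with arm | 0.904 | 7.5% | 0.550 |
| 10% | Overall mean | 1.006 | 4.9% | 0.495 |
| 10% | Regression without arm | 1.005 | 4.9% | 0.495 |

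Formula and simulation agree. Under these assumptions, analysing the observed cases with no imputation is correct on both counts, so each of the four filling methods does worse than no filling.

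**Upper tier.** There is nothing to compute, because no method is fixed. Multiple imputation and the multilevel model on all visits were not simulated.

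**The case against.** **Single imputation and 30% dropout.** A reader might infer that 30% of month-12 values will be mean-filled. By the formula above, a ratio of 0.70 would take type I error to about 17%. The text does not support this. The same sentence turns to multiple imputation above 10%, so that figure would arise only if multiple imputation were considered, rejected and replaced by within-arm filling, and no such step is stated.

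**Outcome-dependent loss.** The Suspension criteria include "Serious adverse events or unusual changes in clinical test results", and a reader might infer that participants with rising glucose will leave and be replaced by an average. The article defines no glucose threshold and does not say that month-12 measurement ends on suspension. Any figure for this bias would rest on invented inputs.

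**Unstated detail.** The article refers to a pre-specified analysis plan that is not shown. Predictors, filling by arm or overall, and the firm trigger for multiple imputation could be there. Regression imputation could also use earlier visits, and if these predict month 12 strongly the SE would be understated by less. A residual draw would restore the spread of the data, though not the lost information. All of this stands as a limit on the size of the problem. It does not remove it, because mean imputation is promised outright and that is a choice already made, not a detail left for later.

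**Small consequences.** The two harms are alternatives, and each is bounded at about 10% in the tier where the plan commits. Overall-mean filling hardly changes power either: 98.6% against 98.7% for observed cases at 10% missing in the simulation. This also stands. It is why the claim that the intention-to-treat result would be invalid goes too far.

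**Conclusion.** The point holds at moderate size. Where the plan commits to single imputation, at 10% missing or less, one of two errors follows. Either the SE is understated by up to about 10%, with type I error of 6.3–6.5% at 5% missing and 7.5–7.8% at 10%, or the effect is shrunk by up to about 10% with type I error near 5%. Where the trial expects the month-12 outcome to lie, at 30%, no method is committed.

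The figures assume deterministic filling, equal loss by arm, and data missing completely at random. The simulation also assumes a correlation of 0.5 and a single month-12 analysis adjusted for baseline, not the multilevel model; the 1 − m ratio depends little on the correlation. The upper-tier conclusion assumes that dropouts lack a visit 4 value. This should be corrected before unblinding, but it is not a fault that by itself undermines the trial.

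**What to change.** In the Statistical analysis section and in the analysis plan:

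1. Delete mean imputation and single regression imputation for outcomes.
2. Make the primary analysis the multilevel model already named, fitted by likelihood to all observed visits, with the arm difference in change from visit 0 to month 12 as the contrast. This matches the Outcomes section, uses the earlier visits of participants who leave early, and is valid if data are missing at random.
3. Commit to multiple imputation, with arm and earlier-visit values in the imputation model, as the sensitivity analysis whatever the missing rate. The 10% boundary then has no role.

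The cost is wording and a little more analysis work; no visit, measurement or suspension criterion changes. Intervals become wider than under within-arm filling. In the simulation, observed-case against arm-mean model SE was 0.1258 / 0.1205 = 1.04 at 5% missing and 0.1293 / 0.1182 = 1.09 at 10%, so about 4% and 9% wider. That is the width the data support.

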### Adverse effect evaluation

The Recommended Daily Allowance (RDA) of zinc is 11 mg in adult males and 8 mg in females [18]. In addition, it has been shown that the therapeutic window for zinc is between 9–40 mg. Hence, 20 mg of elemental zinc is a safe dose for humans. However, in the event of a probable adverse reaction, the following precautions would ensure timely identification and management of patients:

•Reporting mechanisms will be put in place to ensure direct reporting of probable adverse events to the investigator by patients (via telephone, which will be available 24 h on all days).

•During follow-up visits, probable adverse events will be noted by history and examination and investigated in detail. All adverse effects observed will be documented in the case record form (CRF) (Additional file 1).

•All serious adverse events will be reported to the Ethics Review Committee, Faculty of Medicine, University of Colombo, and the National Pharmaco-vigilance Unit of the Department of Pharmacology, Faculty of Medicine, University of Colombo.

•A Data Safety Monitoring Board (DSMB) identified by the investigators will evaluate all the adverse events at regular intervals

•Investigations including liver function, renal function, and FBC will be assessed as detailed above.

•Termination of study: In the event of major adverse effects occurring in a significant proportion of the study population, the study would be terminated pending further investigation.

### Data collection

Data collection will be performed according to the standard operating procedures by medically trained research assistants (RAs).

### Data and biological sample handling

Data will be entered by a minimum number of dedicated staff and saved in a dedicated computer with password protection. Blood samples will be stored in a secure facility with redundant measures to ensure specimens are kept in compliant conditions at all times when in storage. Storage technologies with the capability of monitoring the temperature of samples around the clock will be utilized. After each analysis has been completed and with the approval of the principal investigator, the samples stored in the storage facility may be disposed of by the sample custodian. Asample disposal sheet (SDS) will be completed and kept for further reference.

### Ethical approvals

The study has been approved by the Ethics Review Committee (ERC) of the Faculty of Medicine, University of Colombo (EC/11/189). The trial is also registered at the Sri Lanka Clinical Trials Registry (SLCTR/2012/010). The study will be conducted in compliance with the Declaration of Helsinki and the Good Clinical Practice (GCP) guidelines.

## Discussion

In this article, we present a clinical trial design to evaluate the effects of zinc supplementation in those with pre-diabetes. To our knowledge this is one of the first randomized controlled trials evaluating the effects of long-term zinc supplementation in pre-diabetes. This study will provide the necessary groundwork for future large-scale multicenter clinical trials. Given the current enthusiasm for using various dietary supplements to improve glycemic control and metabolic parameters in those with dysglycemia, properly designed scientific evaluations are a timely requirement. Furthermore, in animal models and in humans, zinc plays an important role in the regulation of appetite [19]. However, presently there are no well-designed randomized control trials to support/refute this argument. This study will also help to provide information pertaining to appetite changes resulting from zinc supplementation. Appetite regulation could be one of the probable mechanisms responsible for beneficial effects on glycemic control. The result, positive or negative, should provide a step change in the evidence guiding current and future policies regarding dietary supplementation in prevention of diabetes.

## Trial status

Patient recruitment stage.

## Abbreviations

ALT: Alanine aminotransferase;AST: Aspartate aminotransferase;BMI: Body mass index;BUN: Blood urea nitrogen;CRF: Case report form;DBP: Diastolic blood pressure;DSMB: Drug safety monitoring board;ERC: Ethics review committee;FBC: Full blood count;FFQ: Food frequency questionnaire;FPG: Fasting plasma glucose;g-GTP: Gamma-glutamyltransferase;HC: Hip circumference;HDL: High-density lipoprotein;LDL: Low-density lipoprotein;OGTT: Oral glucose tolerance test;RA: Research assistance;RBC: Red blood cell;RDA: Recommended Daily Allowance;SBP: Systolic blood pressure;SDS: Sample disposal sheet;SLCTR: Sri Lanka clinical trial registry;SOP: Standard operating procedure;AS: Visual analog scale;WBC: White blood cell;WC: Waist circumference;WHO: World Health Organization;WHR: Waist: hip ratio
